## Meta-analysis

We will conduct meta-analysis of individual participant data using both one- and two-stage meta-analysis approaches in each age group and combined, and for studies that provided HSV-2 information (1). Each method has advantages and disadvantages. When both methods are used, they can provide valuable complementary information.

We will use two-stage meta-analysis as our primary approach to examine the overall association between HC exposures and HIV acquisition. Using this method, participants in each study are compared directly only with other participants in the same study. The two-stage method is well suited to assess between study heterogeneity. While the method is less suitable for identifying prognostic factors (due to the different sets of covariates measured across datasets), it is possible to assess effect modification.

The one-stage method combines and analyzes data from all studies as if they belong to a single study. Study identity is included in statistical models to take into account the fact that the data are from different studies. The one-stage method might not be a valid option if there is marked heterogeneity between the studies. We will explore the effects of confounding and effect modification using the one-stage method. If there is statistical evidence of confounding, we will include the confounding variables in the two-stage multivariable analysis.

### Two-stage Meta-analysis

**Univariable Analysis**: We will examine the associations between HC exposures and HIV in each study by using Cox proportional hazard regression. The hazard ratio (and 95% CI) will be used as the measure of the HC exposure effect. We will use the two-stage method to examine the association in each study. In the first stage, IPD in each study are analyzed separately to obtain the hazard ratio for each HC exposure vs. non-hormonal group. We then will use the random effects model as the primary method to obtain the weighted combined HC exposure effect on HIV acquisition from all studies. This method assumes that there is a distribution of true hazard ratios. The combined effect therefore represents the mean of the population of true hazard ratios. In addition, we will conduct a sensitivity analysis with the assumption that the true hazard ratio is the same in all studies (using a fixed effect model).

**Multivariable Analysis**: We will conduct two separate multivariable Cox proportional hazard regression analyses for each study controlling for confounding factors. The first multivariable analysis - our primary analysis - will include a common set of confounders that are pre-specified in the study protocol (age, marital status/living with partner, condom use, and number of sexual partners) and/or identified using the one-stage meta-analysis approach for all studies. The second multivariable analysis will include the confounders identified for each study individually, i.e., the best multivariable model based on available data in each individual study. The same random effects model and fixed effect approaches as stated in the univariate analysis will be applied to combine the adjusted hazard ratios to give a weighted overall estimate of the effect of HC exposures on HIV acquisition.

### Heterogeneity Assessment: We will then use those associations to investigate the heterogeneity between studies. First, we will examine between-study heterogeneity in associations between exposures and outcomes visually using forest plots of the summary estimates. We will use two statistics to measure the degree of heterogeneity in this meta-analysis: 1) the Q-statistic for which a p-value <0.10 will be interpreted as statistical evidence of heterogeneity (exceeding what would be expected by chance); 2) the I^2^ statistic and its 95% confidence interval, which describes the percentage of total variation across studies due to heterogeneity other than chance (2).

We will use the I^2^ statistic to classify the degree of between-study heterogeneity into low heterogeneity (I^2^ <50%), mild or moderate heterogeneity (I^2^ between 50-75%), and high heterogeneity (I^2^ > 75%). If we find low between-study heterogeneity, no further investigation of heterogeneity will be done. Otherwise, we will examine potential reasons for between-study heterogeneity using stratification or meta-regression. For example, we will stratify the analysis by study region, participant population (sex worker vs. general population) and HIV incidence in the non-hormonal group. The outcome of this exploration of heterogeneity will determine decisions about the appropriateness of meta-analysis to pool the effect estimates from the component studies.

### One-stage Meta-analysis

We will first use the stratified Cox proportional hazard regression to examine the overall unadjusted associations. This allows the survival curve to differ arbitrarily between studies, while assuming that hazard ratios for the exposures of interest are the same across studies. This result will be compared to the overall effect estimated by the univariable analysis from the two-stage meta-analysis. We will then construct multivariable Cox models (3) stratified by study that include identified confounding factors and/or have been pre-specified in the study protocol (age, marital status/living with partner, condom use, and number of sexual partners), and summarize the HC exposure effects on HIV acquisition. Random effects Cox proportional hazard regressions with studies as clusters will also be conducted for univariate and multivariable analyses. This can be seen as a multilevel model with two levels, which allows the estimation of effects of interest in relation to both study-level and participant-level covariates. The effect of modification between HC and age and HSV-2 infection, respectively, will be examined using the approaches proposed above.

### Sensitivity Analyses

Though this meta-analysis provides high quality individual participant data and valuable information about the exposure effect of HC on HIV acquisition, our approach has some limitations. First, the validity of the results of the meta-analysis is dependent on the risk of bias in the component studies. While the IPD meta-analysis can help avoid problems associated with the analyses and reporting of the component studies, it cannot eliminate bias due to their study design or conduct. For example, systematic differences between participants’ characteristics in the HC exposure groups may occur in the component studies resulting in imbalances in prognostic factors associated with HIV acquisition. In addition, due to the variety of study designs, not all the subgroups and potential confounding variables are available in all component studies. It is also possible that we may be unable to recode variables appropriately across studies. Together, these factors could potentially limit our ability to control for confounding and residual confounding could occur. In addition there are fewer Net-En data available in the component studies than there are data for COCs and DMPA.

We will perform the following sensitivity analyses to examine the robustness of the results of our meta-analyses (Table 1):

1. Based on the risk of bias in HC exposure data, we will stratify and analyze data/studies separately by the following criteria
   1. where data/studies cannot distinguish between progestin-only injectables and implants,
   2. Where data/studies cannot distinguish between Net-En and DMPA injectable contraceptives,
   3. Where data/studies cannot distinguish between COC and POP oral contraceptives.
2. Based on the assessment of the risk of bias of the component study – stratify studies with and without an identified risk of bias (e.g. studies that have retention rates lower than 80% at one year).
3. Based on HC exposure switching – censoring participants at the visit before the first contraceptive method switch.
4. Based on pregnancy status
   1. Include pregnancy as a time-varying covariate (ie. not censoring women at the time of pregnancy)
   2. exclude women who are ever pregnant from the analysis
5. Based on key confounding or risk factor variables – stratify studies that do not measure key confounders in a time-varying manner (e.g. participant risk factors, condom use).

Finally, in consideration of the described potential limitations of our study, we will interpret the results of the meta-analyses cautiously, based on a priori hypotheses.

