### Supplementary Analyses

We will apply the approaches mentioned above to conduct the following supplementary analyses (see Table 1) based on:

1. Condom use: We will conduct an analysis of our primary objectives among the subset of women that report no condom use during the study period.
2. High vs. low incidence study populations: We will conduct a stratified analysis of the HC and HIV association based on stratifying studies with high vs. low HIV incidence in the non-hormonal contraceptive group (using the median as the cutpoint).
3. Women by region (Eastern Africa, Southern Africa and South Africa)
4. Age groups among young women: If there are sufficient numbers of HIV cases among 15-24 year old age group, we will conduct an analysis for the primary objectives based on finer age groups: 15-20 years and 21-24 years (versus women > 25 years).

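### The risk-of-bias, exposure-quality and confounder-measurement sensitivity analyses give separate stratum estimates but fix no contrast between strata; for region a contrast is only optional and depends on I² of at least 50%

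*SAP*

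**What the plan says.** The SAP's Sensitivity Analyses section sets out to examine how robust the results are. Three of its items work by splitting:

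- **Item 1 (quality of the exposure data):** "we will stratify and analyze data/studies separately by the following criteria". The criteria are whether injectables can be told from implants, Net-En from DMPA, and combined from progestin-only pills.
- **Item 2 (risk of bias of the component study):** "stratify studies with and without an identified risk of bias", with one-year retention below 80% as the example.
- **Item 5 (measurement of confounders):** stratify on studies that lack time-varying measures of key confounders.

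None of the three names an interaction term, a meta-regression or a ratio of hazard ratios.

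Region is item 3 of Supplementary Analyses, with three regions. That section opens: "We will apply the approaches mentioned above to conduct the following supplementary analyses". It does not say which approach applies to which item. Heterogeneity Assessment stops if I² is below 50%. Above that, "we will examine potential reasons for between-study heterogeneity using stratification or meta-regression", with region among the examples; the example sentence itself speaks of stratifying.

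The one formal test of a difference in effect is in Effect modification: a likelihood ratio test at p<0.05 for age and for HSV-2, referred to again under One-stage Meta-analysis.

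**The concern.** Whether a result is robust to study quality is a question about a difference: does the hazard ratio in studies at risk of bias differ from that in the others? Two separate hazard ratios do not answer it unless their difference is estimated with its uncertainty. Each stratum has less information than the whole, so one can reach significance and the other miss it even when the effects agree.

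The SAP itself says that the validity of the meta-analysis depends on the risk of bias in its component studies. In a pooled observational analysis, the credibility of a harm signal will turn largely on whether it persists in the better studies. With no contrast fixed in advance, a chance pattern could be used to dismiss a real signal or to suggest a regional one.

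**Working it through.** **Inputs.** From the SAP: 18 studies (Introduction) and hazard ratios with 95% CIs (Two-stage Meta-analysis), taken here as two-sided 5% tests. The SAP gives no number of events, target hazard ratio, power or standard errors, so there is no figure of its own to reproduce. Overall power, split, hazard ratio (HR), within-study SE and between-study SD (tau) below are assumptions, shown over ranges.

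**Step 1: two strata with the same average effect.** Overall noncentrality is δ = 1.96 + z(overall power). A stratum holding share f of the information has noncentrality δ√f and two-sided power p = 1 − Φ(1.96 − δ√f) + Φ(−1.96 − δ√f). The chance that exactly one stratum is significant is p₁(1 − p₂) + p₂(1 − p₁).

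Example: at 90% overall power δ = 1.96 + 1.28 = 3.24. Each half has 3.24 × √0.5 = 2.29, so p = 0.63, and the chance of disagreement is 2 × 0.63 × 0.37 = 0.47.

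| Overall power | 50:50 | 70:30 | 80:20 |
|---|---|---|---|
| No effect | 9.5% | 9.5% | 9.5% |
| 20% | 22% | 22% | 22% |
| 50% | 41% | 42% | 44% |
| 80% | 50% | 55% | 61% |
| 90% | 47% | 54% | 63% |
| 95% | 40% | 50% | 61% |
| 99% | 24% | 37% | 52% |
| 99.9% | 10% | 22% | 38% |

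A 90:10 split at 80-90% power gives 68-74%.

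**Step 2: three equal regions.** The chance that they are not all alike is 1 − p³ − (1 − p)³: 14% with no effect, 49% at 50% overall power, 70% at 80% and 75% at 90%.

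**Step 3: 18 studies, within-study SE 0.25.** The noncentrality of a stratum of k studies is ln(HR)/√((0.25² + tau²)/k).

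| HR | tau | 9/9 | 6/12 | 4/14 |
|---|---|---|---|---|
| 1.0 | any | 9.5% | 9.5% | 9.5% |
| 1.3 | 0 | 21% | 29% | 45% |
| 1.3 | 0.2-0.3 | 43-50% | 49-54% | 59-60% |
| 1.5 | 0.2-0.3 | 6-22% | 13-30% | 28-46% |

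At HR 1.1 with tau 0.2-0.3 the range over these splits is 20-26%. The figure is therefore highest at an intermediate HR and depends on tau.

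**Step 4: error rate of a direct contrast.** Simulation of the step 1 model (400,000 draws per scenario; overall power 50%, 80% and 90%; splits 50:50 and 70:30) gave a falsely significant difference in 5.0% of splits. In the same scenarios exactly one stratum was significant in 41-55%.

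**Step 5: does the I² rule stand in for a contrast?** Take 18 studies with SE 0.25, split 9/9, a true ratio of hazard ratios of 1.4 and no other heterogeneity (all assumed). The contrast has SE 0.25 × √(2/9) = 0.118, so ln(1.4)/0.118 = 2.855 and power is Φ(2.855 − 1.96) = 81%. I² is below 50% when Q is below 2 × 17 = 34, which happened in 86% of simulated runs. In 68% of runs the contrast was significant while I² was below 50%, so the plan would not have looked further.

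**The case against.** Four points on the other side have force.

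- **No rule based on significance.** The SAP nowhere says that strata will be compared by whether each is significant. It reports hazard ratios with intervals, forest plots, Q and I², and promises cautious interpretation. Setting stratum estimates beside the primary estimate is an ordinary reading of a robustness check. This stands. A reader might infer that the plan has a built-in 40-60% error rate, but the documents do not support that: the rate describes a possible misreading, not a planned decision.
- **The size depends on unstated inputs.** A reader might also infer that equal true effects alone produce 40-60%. They do not. With HR 1.3, tau 0 and SE 0.25 the rate is 21-45%, with no effect it is 9.5%, and three regions need a different calculation. This stands too.
- **Region is not wholly without a contrast.** Heterogeneity Assessment offers meta-regression and names region, and Supplementary Analyses carries earlier approaches over. A claim that no regional contrast exists would go too far. But stratification alone satisfies the SAP's wording, and nothing is required below I² of 50%.
- **A ratio has limits.** Item 1 may split data within studies, where a regression of study-level estimates does not fit, and its strata measure different exposures. With 18 studies, and fewer Net-En data, many ratios will be imprecise. This shapes the fix but does not remove the need for it.

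Table 1 classes all these analyses as sensitivity or supplementary, so the primary estimates and the age and HSV-2 tests are untouched.

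**Conclusion.** The gap is real but limited. Items 1, 2 and 5 assess robustness through separate stratum estimates and fix no contrast; for region a contrast is optional and conditional on I². The I² rule is a weak substitute: under the step 5 assumptions it would usually pass over a difference that a direct contrast detects.

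If readers fall back on significance by stratum, chance disagreement is roughly 40-60%. That holds for two not very unequal strata with a real common average effect and about 50-95% overall power. Outside those conditions it ranges from 9.5% with no effect to 74% for a 90:10 split at 90% power. None of the inputs comes from the SAP. This is a worthwhile improvement to the sensitivity and supplementary analyses and does not challenge the primary result.

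**What to change.** Add to Sensitivity Analyses items 1, 2 and 5 and to Supplementary Analyses item 3, to apply whatever the I²:

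> For each split, the ratio of pooled hazard ratios between strata will be reported with its 95% CI beside the stratum estimates. Where strata are whole studies, it will come from random-effects meta-regression of the study log hazard ratios on stratum; where a split runs within studies, from a stratum-by-HC interaction in the one-stage model. Neither a difference nor its absence will be inferred from significance within strata, and a wide interval will be reported as inconclusive, not as robustness.

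For item 1, add that the ratio also reflects a different exposure definition and so does not isolate bias. For region, report ratios against a named reference region.

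The cost is one further model per split, on estimates or data already in hand. The downside is imprecise intervals, especially for Net-En, which is a fair statement of what 18 studies can show.

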### Supplementary Analyses

We will apply the approaches mentioned above to conduct the following supplementary analyses (see Table 1) based on:

1. Condom use: We will conduct an analysis of our primary objectives among the subset of women that report no condom use during the study period.
2. High vs. low incidence study populations: We will conduct a stratified analysis of the HC and HIV association based on stratifying studies with high vs. low HIV incidence in the non-hormonal contraceptive group (using the median as the cutpoint).
3. Women by region (Eastern Africa, Southern Africa and South Africa)
4. Age groups among young women: If there are sufficient numbers of HIV cases among 15-24 year old age group, we will conduct an analysis for the primary objectives based on finer age groups: 15-20 years and 21-24 years (versus women > 25 years).

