**FHI 360**

**Hormonal Contraception and the Risk of HIV Acquisition: An Individual Participant Data Meta-Analysis**

**(HC-HIV Meta-analysis)**

**(NICHD award number R21HD069192/ FHI 360 Study # 10263)**

**Detailed Statistical Analysis Plan**

# INTRODUCTION

This study is a meta-analysis of individual participant data (IPD) from 18 prospective longitudinal studies. The main aim of the IPD meta-analysis is to determine whether hormonal contraception, including combined oral contraceptives (COCs) and the progestin-only injectables DMPA and Net-En increase women’s risk of acquiring HIV infection. We will compare the rate of HIV acquisition among women who use COCs, DMPA and Net-En with the rate among women who do not use hormonal contraception. This statistical analysis plan is an extended version of the statistical analysis plan from *HC-HIV IPD Meta-Analysis Protocol - Statistical Analysis Plan 0.95*. This analysis plan provides details on analysis strategy, variable construction and statistical testing procedures.

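### Splitting studies by observed HIV incidence in the non-hormonal group biases the high- versus low-incidence contrast, because that rate is also the reference of every hazard ratio

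*SAP*

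**What the plan says.** The Introduction describes "individual participant data (IPD) from 18 prospective longitudinal studies". Under Two-stage Meta-analysis, the first stage analyses each study separately to "obtain the hazard ratio for each HC exposure vs. non-hormonal group", and the second stage will "use the random effects model as the primary method to obtain the weighted combined HC exposure effect".

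The NH group's incidence then appears twice as a study-level stratifier:

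- Supplementary Analyses, item 2, compares the association between halves formed by "stratifying studies with high vs. low HIV incidence in the non-hormonal contraceptive group (using the median as the cutpoint". Table 1 marks this analysis as supplementary.
- Heterogeneity Assessment lists, among its examples of stratifiers, "participant population (sex worker vs. general population) and HIV incidence in the non-hormonal group". This applies only when I² is not low: "If we find low between-study heterogeneity, no further investigation of heterogeneity will be done". Of the exploration as a whole it says: "The outcome of this exploration of heterogeneity will determine decisions about the appropriateness of meta-analysis to pool the effect estimates from the component studies".

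Neither place names an incidence measure from outside the study data, or a method that allows for sampling error in the NH rate. The only caution is general: "we will interpret the results of the meta-analyses cautiously, based on a priori hypotheses".

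**The concern.** One observed quantity does two jobs: it is the reference rate of the study's HR, and it decides which half the study falls in. Chance error in the NH rate moves both at once, in opposite directions. The expected contrast between halves is then not zero when there is no true difference, and its direction is known in advance: a lower HR where incidence is high.

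Two readings are at stake. The supplementary table could suggest that contraception is relatively more harmful in low-incidence populations, or could mask a true difference the other way. In the heterogeneity section, incidence could appear to explain spread between studies that is partly this artefact. Because each contraceptive is compared with the NH group, the artefact points the same way for COCs, DMPA and Net-En. Agreement across the three would therefore not be independent confirmation.

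**Working it through.** **No plan figure to reproduce.** The SAP gives 18 studies, the stratifier, the median cutpoint and the reference group. It gives no NH infection counts, no spread of incidence and no test between halves. Everything else below is an assumption.

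**Approximation.** Let *a* be the NH infections in a study and *s* the between-study SD of true log incidence. Treat the log HR as a log rate ratio with one true value in all studies.

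- Variance of the observed log NH rate: s² + 1/a
- Covariance of the log HR with the observed log NH rate: −1/a
- Slope induced by chance: −(1/a) / (s² + 1/a)
- Mean gap in log NH rate between halves of a normal sample split at the median: 1.596 × √(s² + 1/a)
- Spurious high/low HR ratio: exp(slope × gap)

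With a = 30, s = 0.3: slope = −0.0333/0.1233 = −0.270; gap = 1.596 × 0.351 = 0.560; ratio = exp(−0.151) = 0.86.

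With a = 100, s = 0.5: slope = −0.010/0.260 = −0.0385; gap = 1.596 × 0.510 = 0.814; ratio = exp(−0.031) = 0.97.

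**Simulation with a common HR.** 18 studies, true HR 1.30, Poisson infections, equal person-time in the two groups unless noted, DerSimonian-Laird pooling in each half, z-test between halves at two-sided 0.05. Ranges cover several runs that differed in detail.

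| NH infections per study | s | High/low HR ratio | False positives |
|---|---|---|---|
| 8–60 | 0.3 | 0.84–0.88 | 17–22% |
| 8–60 | 0.5 | 0.89–0.92 | about 9% |
| 50–150 | 0.3 | 0.95 | 9–10% |
| 50–150 | 0.5 | 0.97 | 5% |
| 50–150 | 1.0 | 0.98–0.99 | 4% |

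Stratifying on true incidence gives 1.00 and about 3–4% in these settings. With half the person-time in the contraceptive group, the first row has 14.5% false positives. In a separate run (true HR 1.0, half the person-time, study size varying), the extreme case of no true spread (s = 0) and 20 NH infections gave 0.72 and 36%.

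**Check on the simplest substitute, whole-study incidence.** With a common HR it removes the bias. With true HRs that vary (SD *tau* on the log scale), a high HR raises whole-study incidence. At HR 1.30 and equal person-time, log incidence moves with log HR at a rate of 1.30/2.30 = 0.565. Simulated with mean HR 1.30, and HRs unrelated to baseline incidence:

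| NH infections | s | tau | NH stratifier | Whole-study stratifier |
|---|---|---|---|---|
| 8–60 | 0.3 | 0.3 | 0.83–0.86, 16% | 1.23, 21–23% |
| 8–60 | 0.5 | 0.5 | 0.85–0.91, 10–12% | 1.41–1.43, 31–33% |
| 50–150 | 0.3 | 0.5 | 0.94, 8% | 1.65–1.68, 69–71% |
| 50–150 | 1.0 | 0.3 | 0.97–0.98, 8% | 1.07–1.08, 10% |

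True incidence gives 0.98–1.00 and 6–8% here. The NH bias shrinks as infections accumulate. The whole-study bias does not, because it comes from the true HRs and not from sampling error.

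**The case against.** The case for leaving the plan alone has real parts:

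- **The bias may be small.** With 50 to 150 NH infections per study and s of 0.5 or more, the contrast is off by 3% or less and the false-positive rate is near nominal. Studies of sex workers and general populations in several regions could well differ that much in incidence. This stands, but it is an assumption that the SAP does not let a reader check.
- **The reach is limited.** Item 2 is supplementary and has no interaction test or decision rule. In the heterogeneity section, NH incidence is one example beside region and population. This stands. A reader might infer that the primary pooled HR is biased; it is not, since it does not use the split.
- **NH incidence is a sensible measure of baseline risk**, because exposure effects do not contaminate it. This also stands. The fault is in using the observed rate as if it were free of error, not in the choice of baseline risk.
- **Meta-regression is already allowed.** This helps only if the error is modelled. An ordinary meta-regression on the observed NH rate has the same induced slope as shown in the working.
- **Cautious interpretation is promised.** The statement is generic and does not alert anyone to a bias of known direction.

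A reader might also infer that a false difference is bound to appear. The documents do not support that: the expected contrast is shifted, but whether a given dataset shows a visible difference depends on counts and spread that the SAP does not report.

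**Conclusion.** The point holds as a one-directional, uncorrected bias of unknown size in a secondary part of the plan. It ranges from material (a high/low HR ratio near 0.85, roughly one false positive in five) with sparse NH infections and similar incidences, to negligible (0.97 or closer to 1, about 5%) with many infections and well-spread incidence. These figures rest on assumed counts, spread, person-time and a common HR, and on crude rate ratios standing in for Cox estimates.

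The more consequential use is in Heterogeneity Assessment, where the exploration informs whether pooling is appropriate. It would go too far to say the plan will reach a wrong pooling decision: the stratifier is only one input, and it is used only when I² is 50% or more. The change is worth making before the analysis is run.

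**What to change.** In both Supplementary Analyses item 2 and Heterogeneity Assessment, replace the median split on observed NH incidence with one of these:

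1. A meta-regression of log HR on *underlying* NH log incidence, fitted as a bivariate or hierarchical model. Each study supplies its log NH rate and log HR with their sampling variances and their covariance (about −1/a). The slope relates the true HR to the true NH incidence. Report it with its confidence interval and, for readability, the fitted HR at a low and a high incidence fixed in advance.
2. Stratification on an incidence measure external to the data that form the HR, with its source and cutpoint named in advance.

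Do not substitute whole-study incidence. The primary model allows true HRs to vary, and the heterogeneity exploration starts only when observed heterogeneity is not low. With varying HRs, the simulated whole-study contrast was biased in the opposite direction, by ratios of about 1.2 to 1.7 at tau 0.3–0.5 and s 0.3–0.5.

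If a two-group table on NH incidence is kept for description, label it as subject to this bias, give NH infections per study, and do not use it to judge pooling.

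Cost: the first option needs no new data, only some extra modelling and a less simple presentation than two groups; with 18 studies the slope may be imprecise. The second option needs a suitable outside source.
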